## Results

### Descriptive

The means and standard deviations (*SDs*) of the ratings across the Norwegians and US coders are presented in Supplementary material on page 21.

### Inter-rater reliability of NB rating

Table 1 Inter-rater reliability tests using Cronbach's α and intra-class coefficients (Cicchetti, 1994) showed high internal consistency in NB coding between coders both in the Norwegian and the US groups.

**Table 1 T1:** Cronbach's α and intra-class coefficients between the coders across coding groups and items.

**Coding items**	**Norwegian α**	**The US α**	**Norwegian ICC**	**The US ICC**
Gesture	0.99	0.98	0.99	0.98
Smile	0.99	0.92	0.99	0.96
Eye contact	0.99	0.86	0.99	0.92
Positivity in tone of voice	0.97	0.86	0.96	0.86
Dominance	0.83	0.85	0.82	0.66
Overall positivity	0.98	0.91	0.97	0.85
Expressiveness	0.98	0.93	0.96	0.91

ICC, intra-class coefficients using two-way mixed effects model. Cronbach's α: values ≥ 0.70 = acceptable reliability. ICC: values ≥ 0.60 = acceptable reliability. N of Norwegian coders: 15; N of the US coders: 6.

### Inter-rater reliability between actors

The inter-rater reliabilities of the coders for both the Norwegian and the US coders on NBs acted by actors were ≥ 0.72 for both Cronbach's alpha and ICC values.

### Differences in NB ratings between countries

The US sample had significantly higher ratings of smile [Norwegian mean rank (*MR*) = 8.67, US *MR* = 16.83, *H*(2) = 7.49, *P* = 0.006], tone of voice [Norwegian *MR* = 8.83, US *MR* = 16.42, *H*(2) = 67.41, *P* = 0.01], dominance [Norwegian *MR* = 8.90, US *MR* = 16.25, *H*(2) = 6.04, *P* = 0.01], positivity [Norwegian *MR* = 8.80, US *MR* = 16.50, *H*(2) = 6.61, *P* = 0.01], and expressivity [Norwegian *MR* = 8.67, US *MR* = 16.83, *H*(2) = 7.43, *P* = 0.006].

### Differences in NB ratings between actors

The second K–W test showed that the actors were rated similarly in gestures, eye contact, smile, tone of voice, dominance, expressivity, and overall positivity (*P* > 0.058); however, actor 1 had more gestures [*H*(2) = 10.92, *P* = 0.004] and eye contact [*H*(2) = 7.28, *P* = 0.02] than the other two; and actor 3 smiled more [*H*(2) = 16.34, *P* = 0.001]. Actors were rated differently regarding the attractiveness [*H*(2) = 19.40, *P* = 0.001].

### Construct validity of the manipulated NB conditions

There were no differences in the rating of NBs between the introduction, calibration, and pre-test (see Supplementary Table on page 21). Therefore, these phases are not analyzed further.

As expected, the +BM had higher gestures than the other conditions [*F*_(3, 18)_ = 225.74, η^2^ = 0.97]. The +FE had higher eye contact [*F*_(3, 18)_ = 97.29, η^2^ = 0.94] and smiles [*F*_(3, 18)_ = 127.96, η^2^ = 0.95] than the other conditions. The +TV had higher positivity in tone of voice than the other conditions [*F*_(3, 18)_ = 64.56, η^2^ = 0.91]. The +BM and +TV had higher smiles than the NC (*P*s < 0.001), and the +FE and +BM had higher positivity in tone of voice than the NC (*P*s < 0.001). The +FE was more positive in tone of voice compared to the +BM (*P* = 0.003), and the +BM had higher eye contact compared to the +TV (*P* = 0.049) (Figure 3).

**Figure 3 F3:**
[figure not shown]
Amplitude of NBs in each NB condition. TV: positive tone of voice condition; FE: positive facial expression; BM: positive body movements; NC: neutral condition.

### Effects of micro-level NBs on dominance, expressivity, and positivity

#### Dominance

The significant main effect of Condition [*F*_(2.02, 40.56)_ = 7.57, η^2^ = 0.27] was due to higher dominance in the +FE (*P* = 0.003) and +BM (*P* = 0.007) compared to the NC. There was also higher dominance in the +FE (*P* = 0.009) and +BM (*P* = 0.020) compared to the +TV. No other comparisons were significant.

#### Overall positivity

The significant main effect of Condition [*F*_(2.55, 51.09)_ = 53.26, η^2^ = 0.72] was due to higher overall positivity in the +TV (*P* = 0.0002), +FE (*P* = 0.0002), and +BM (*P* = 0.0002) compared to the NC. There was also higher overall positivity in the +FE compared to the +TV (*P* = 0.041) and the +BM (*P* = 0.0002). No other comparisons were significant.

#### Expressivity

The significant main effect of Condition [*F*_(2.91, 58.34)_ = 58.06, η^2^ = 0.74] was due to higher expressivity in the +TV (*P* = 0.0002), +FE (*P* = 0.0002), and +BM (*P* = 0.0002) compared to the NC. There was also higher expressivity in the +BM compared to the +TV (*P* = 0.0002) and the +FE (*P* = 0.008). No other comparisons were significant (Figure 4).

**Figure 4 F4:**
[figure not shown]
Amplitude of dominance, positivity, and expressivity in NB conditions. TV: positive tone of voice; FE: positive facial expression; BM: positive body movements; NC: neutral condition.

## Discussion

The main findings were that first, both the NB video conditions and the NB coding log held acceptable reliability and construct validity, and second, all three positively enhanced NB conditions increased ratings of overall positivity and expressivity compared to the neutral condition. A positive tone of voice did not increase ratings of dominance compared to neutral NBs, but positive facial expressions and positive body movements did. Positive facial expressions increased ratings of overall positivity more than the other positive NBs. Positive body movements, on the other hand, increased ratings of expressivity more than the other NBs.

The moderate-to-high internal consistency and intra-class coefficients between the coders on the ratings of NBs suggested that the scale was successful at screening both the micro- and macro-level NBs, implying that simple NB rating scales that rely on general impressions can reliably capture the amplitude of NBs at both micro- and macro-levels (Blanch-Hartigan et al., 2018).

Regarding the ICC values, coders had acceptable levels of reliability; however, reliability was lower for ratings of dominance (≥ 0.66). The coders had medium-to-high consensus in ratings of NBs between actors. The overall results support the similarity in NBs between the actors, although individual differences in the expression of NBs existed, mostly in the amplitude and extent of the NBs, and therefore, not likely to damage the consistency. Moreover, this level of variability may be a characteristic of non-verbal communication, as an NB, for instance a smile, cannot be identical between two persons. Therefore, we believe that for ecological validity, this type of difference is acceptable and important for generalizability.

Even though the US group rated the NBs more positively than the Norwegian group did, both coding groups rated the micro- and macro-level NBs in the same direction. This is in line with research showing that the similarity in perception and judging of NBs is pancultural (e.g., that a smile is usually a positive NB in most cultures) (Ambady et al., 2000; Elfenbein and Ambady, 2002; Matsumoto, 2006a). However, the US coders had higher ratings than the Norwegian coders did, which is in line with documents suggesting that the judgment about the intensity of expressed NBs might vary across cultures (Ekman et al., 1987).

There were differences in the rating of physical attractiveness between actors, and physical attractiveness can affect social interactions (Reis et al., 1980, 1982) and placebo effects (e.g., Yan et al., 2018). The main aim of this experiment is to test the effects of the NBs of caregivers on the amplitude of pain reports and placebo effects. Therefore, to control for the effects of attractiveness, two actors with the higher and lower ratings of physical attractiveness will be used in each NB group of the +FE, +TV, +BM, and the NC. Thus, participants in each group will either see the actor with a higher rating or lower rating of attractiveness, and the sum of the two sub-groups will be used in the analyses. This approach may control for the confounding effects of attractiveness.

The NBs were expressed as intended. That is, the +FE had more smiling and eye contact, the +TV had higher positivity in tone of voice, and the +BM had more positive body movements and gestures compared to the NC and other conditions. The introduction, calibration, and pre-test were like the NC, having the lowest rates of NBs. This indicates that the NBs were as they were intended to be. So, in neutral conditions (introduction, calibration, pre-test, and the NC), the NBs were low as intended, and in positive conditions (+FE, +TV, and +BM), the NB(s) that were at the focus had the highest level, confirming the validity of the NB conditions. However, in positive NBs, NBs other than the NB of the focus increased as well. For example, in +BM, which had the highest gestures, eye contact was also increased. This can be due to the quality of the NBs, as some NBs can affect the other NBs (Dittmann, 1972); for example, tone of voice is affected when a welcoming body posture or a leaning forward is expressed (Dittmann and Llewellyn, 1969). Similarly, an increase in smiling was observed in the +TV, which can be partly explained by the physiological structure of the muscles involved in the production of certain NBs, such as the tone of voice and its effects on facial expressions (e.g., Campanella and Belin, 2007). However, the NBs of the focus were still the highest among the other NBs, confirming the validity of the NB manipulations.

Moreover, the increase in other NBs along with the NB of the focus suggests that the harmony between the NBs was not damaged, as even though the NB of the focus was enhanced more than the other NBs, the other NBs were accordingly increased too. Therefore, the manipulations are not likely to have produced incongruency between NBs. It has been shown that the incongruency between the communication channels (verbal and non-verbal) hinders the transmission of the message and emotions (Gorawara-Bhat et al., 2017), but the incongruency between the NBs has not been investigated very much. In a separate study, we tested whether the enhancement of NBs in current videos produced incongruency between the NBs, and the preliminary results showed no incongruency between NBs in present NBs (see Fjørstad, 2022; Nygård, 2022; Rishovd, 2022; bachelor theses).

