**Figure 2 F2:**
[figure not shown]
Experimental procedure. Gray boxes, neutral NBs are displayed by VEs; VE1, the first videotaped experiment that shows only neutral NBs; VE2, the second VE that has either positive or neutral NBs. +FE: positive facial expressions; +TV: positive tone of voice; +BM: positive body movements; NC: neutral condition. During the calibration, the intensity of the thermal pain (illustrated by a thermometer) will be calibrated to the individual average of pain intensity using three ascending stimulations. During the pre-test, the individually calibrated painful stimulation will be induced. Next, participants will be randomly assigned to one of the four groups. During the conditioning, a placebo cream will be applied with suggestive information from the VE2, and unbeknownst to the participant, the pain stimulation will be lowered from an intensity of “5” to “3.” In the +FE positive facial expressions, in the +TV positive tone of voice, in the +BM positive body movements, and in the NC, neutral NBs will be displayed by VE2. Each group will have two VE2s, and the participants will be randomly assigned to one of them. The post-test is identical to conditioning, with the only difference that the stimulation intensity of “5,” the same as in the pre-test, will be induced in the post-test. The pain intensity and unpleasantness will be recorded at 30 s, 2 min, and 4 min of the stimulation, and the stress and arousal will be recorded before and after the stimulations.

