### Design

We propose a mixed design with four Groups (+FE, +TV, +BM, and NC; as between factors) × 3 Timepoints (first at 30 s, second at 2 min, and third timepoint at 4 min of the stimulation), with the covariate effects of participant sex with two levels, and the knowledge of the assistants with two levels (CI and UI).

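### VE2 actor is randomised within every NB group but pooled away in the analysis. Adding it as a model term would recover some precision and show whether effects appear with both actors, at almost no cost.

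*Protocol article*

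**What the plan says.** All references are to the protocol article.

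- **Allocation (Figure 2 legend).** "Each group will have two VE2s, and the participants will be randomly assigned to one of them". VE2 delivers the conditioning and post-test phases, so the actor is the person who carries the manipulation.
- **Purpose (Discussion).** Because attractiveness may affect placebo responses, every NB group, NC included, has one actor rated higher on it and one rated lower. The Discussion says this may control for confounding by attractiveness.
- **Analysis (Discussion).** "the sum of the two sub-groups will be used in the analyses".
- **Model (Design).** "We propose a mixed design with four Groups (+FE, +TV, +BM, and NC; as between factors", crossed with three timepoints, "with the covariate effects of participant sex with two levels, and the knowledge of the assistants with two levels". Actor is not listed, and the Statistical analysis section adds no actor term.
- **Actor ratings (Differences in NB ratings between actors).** "Actors were rated differently regarding the attractiveness" (P = 0.001). Also, "actor 1 had more gestures" (P = 0.004) and more eye contact (P = 0.02) than the other two, and actor 3 smiled more (P = 0.001). The same paragraph first says that the actors were rated similarly on these items (P > 0.058), so it does not fully agree with itself.

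**The concern.** VE2 actor is a second randomised factor, crossed with NB group. The plan models another personal influence in the room, what the assistant has been told, but not the actor who expresses the behaviours under study.

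The protocol's own ratings suggest that the actor could matter. Gestures belong to the +BM script, and smiling and eye contact to the +FE script. The article does not say which two of the three actors serve as VE2. On the differences it reports, any pair differs on at least one manipulated behaviour:

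- actors 1 and 2 on gestures and eye contact;
- actors 2 and 3 on smiling;
- actors 1 and 3 on all three.

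No actor difference in tone of voice is reported.

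Two things are at stake. The first is precision: any actor effect on pain stays in the residual of a study that is already small. The second is interpretation: a pooled NB estimate cannot show whether the effect appears with both actors or mainly with one.

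**Working it through.** **Inputs from the protocol article**
- 80 participants, 20 per NB group (Participants).
- Planning effect 0.478, alpha 0.05, power about 0.5 (Statistical power).
- Two VE2 actors per group (Figure 2 legend).

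**Assumed, because the documents give no value:** the actor difference in pain change, a, in units of the within-actor SD. The range shown is 0.2 to 0.8.

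**1. Planning figures.** The pooled SD is √[(1.52² + 1.37²)/2] = 1.447, so d = (3.42 − 2.73)/1.447 = 0.477, which agrees with 0.478. A two-sided t test of 20 v 20 has noncentrality 0.478/√(2/20) = 1.51 and power 0.313. This is below the stated 0.5. That gap is a separate matter; 0.313 serves here only as the reference value for a contrast with actor in the model.

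**2. Variance left in the error term.** With two actors used equally, an actor difference a adds a²/4 to the residual variance. For a = 0.2, 0.5 and 0.8 this is 1%, 6% and 16%.

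**3. Effect on the test.** Simulated 20 v 20 contrast, two-sided 0.05, actor split 10/10 in each group:

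| Assumed a (SD) | Type I error, actor omitted | Power, actor omitted | Power, actor in model |
|---|---|---|---|
| 0.2 | 0.048 | 0.309 | 0.313 |
| 0.5 | 0.043 | 0.290 | 0.313 |
| 0.8 | 0.034 | 0.259 | 0.313 |

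The loss is 0.4 to 5.4 percentage points of power. The pooled test is slightly conservative, not liberal.

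Under simple (unrestricted) allocation with a = 0.5, omitting actor gives type I error 0.050 and power 0.297.

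**4. Chance imbalance, if allocation is simple.** The article does not state how VE2 is allocated beyond random assignment.
- The share of a group seeing one given actor has SD √(0.25/20) = 0.112.
- A pairwise contrast therefore shifts with SD a × √2 × 0.112. For a = 0.5 this is 0.08 SD.
- A 14/6 v 6/14 split shifts the contrast by 0.5 × (0.7 − 0.3) = 0.20 SD, or 0.20/0.478 = 42% of the planning effect.
- This is a tail event. With p = P(X ≤ 6) = 0.0577 for Binomial(20, 0.5), opposite splits at least this extreme have probability 2p² = 0.0066 for a given pair of groups. For any pair among the four groups it is 1 − 2(1 − p)⁴ + (1 − 2p)⁴ = 0.035.

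**5. Could an actor-by-NB interaction be tested?** With 10 per cell, a difference of differences has standard error √(4/10) = 0.632 SD. Power is 0.11 for an interaction of 0.478 SD and 0.31 for 0.956 SD (twice the planning effect). Actor-specific estimates can only be descriptive.

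**The case against.** The strongest defence is that the design already does what it claims. Both actors appear in every NB group and participants are randomised between them, so attractiveness is balanced across groups in expectation. The article says only that this may control for it. Omitting a crossed, randomised factor leaves the contrast unbiased and the test valid. The authors also considered actor differences: the Discussion accepts them for ecological validity and generalizability, and Expected limitations lists attractiveness. The ratings come from video coders rather than from pain outcomes, and the paragraph reporting them is not consistent. All of this stands, and it limits the point to precision and reporting.

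A reader might infer stronger claims that the documents do not support:

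- **That NB contrasts are confounded by actor.** They are not, because actor is crossed with group.
- **That error variance and chance imbalance are two separate harms.** Under simple allocation the pooled standard error already reflects the imbalance, and type I error stays at 0.050.
- **That a shift of 42% of the planning effect is likely.** It rests on an assumed 0.5 SD actor difference and a split with probability 0.0066 for a given pair of groups.
- **That the lack of a stated even split is an error.** A condensed article commonly leaves such allocation detail to the full protocol.
- **That type I error is inflated.** This would follow only if inference were meant for actors beyond these two and NB effects varied by actor. The documents give no such variance, and a fixed actor term would not address it.

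What the defence does not answer is why a factor that is randomised and known for every participant should be left out of the model.

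**Conclusion.** The point holds as a free improvement. Pooling the two actor sub-groups is valid for these two actors but gives up information the design collects. The cost is about 0.4 to 5 percentage points of power for a 20 v 20 contrast, resting on assumed actor differences of 0.2 to 0.8 SD, normal outcomes and an even split. If actor has no effect on pain, nothing material is lost. If allocation is simple, the typical chance shift at an assumed 0.5 SD is about 0.08 SD, and the model term would adjust for it. The reporting gain does not depend on the assumed size: without estimates by actor, a reader cannot see whether an NB effect appears with both.

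**What to change.** Replace the Discussion's statement that "the sum of the two sub-groups will be used in the analyses" with three commitments, and add the actor term to the Design section:

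1. VE2 actor (two levels) enters every subjective and physiological model as a fixed factor.
2. NB estimates are also shown separately by actor, labelled descriptive, with no interaction test used for conclusions.
3. Where allocation is still open, VE2 actor is balanced within each NB group.

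The cost is one degree of freedom and a few lines of text, plus one more balanced factor in the allocation list if the third item is still possible. The first two items need no new data.

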### Effects of NBs on the impressions of dominance, overall positivity, and expressivity

Positive facial expressions, tone of voice, and body movements contributed to the impressions of overall positivity and expressivity, and positive facial expressions and body movements contributed to the impressions of dominance, whereas positive tone of voice did not, as compared to the NC.

This means that overall positivity and expressivity may be transmitted by the NBs of facial expressions, body movements, and tone of voice. Therefore, a longer gaze, more smiling, more positive and expressive body movements and gestures, and a more positive tone of voice will make the individual appear more positive and expressive. In most of previous studies, static photographs of caregiver's facial expressions are used to test the perceived impressions (Kraft-Todd et al., 2017; Necka et al., 2021); however, in this study, dynamic NBs of caregivers in three dimensions of facial expressions, body movements, and tone of voice are tested, with the results showing that higher display of such NBs, regardless of the type, contributes to the impression of overall positivity.

Facial expressions received the highest ratings of overall positivity, which is in line with previous research (e.g., Tickle-Degnen and Rosenthal, 1990; Ambady et al., 2002a) showing the role of facial expressions in the transmission of emotions. However, other positive NBs also increased the overall positivity, contradicting studies suggesting facial expressions are the only NBs to transmit positivity (e.g., Zuckerman, 1986). Our results suggest that a warmer tone of voice and open and expressive body movements contribute to perceived positivity as well as more positive facial expressions. Harrigan and Rosenthal (1983) showed that subtle changes in the body postures of clinicians, for example in their trunk angle and arm position, changed the perceived ratings of warmth, as clinicians who leaned forward more, nodded more, and had open arm positions were perceived more positively.

All positively enhanced NBs contributed to the impression of expressivity. This means that more positive facial expressions, a warmer tone of voice, and more body movements were perceived as more expressive. Moreover, positive body movements received the highest ratings of expressivity compared to all other conditions. Ekman and Friesen (1967) showed that body movements and gestures facilitated the transmission of the intensity and amplitude of that emotion, and our results showed that the body movements made the caregiver be perceived as more expressive. Therefore, our results suggest that first, adding more NBs, regardless of the type, can add to the expressivity, and second, positive body movements can be the NB that increases the expressivity the most.

Facial expressions and body movements contributed to the rating of dominance, but a positive tone of voice did not. The +FE and the +BM were both rated as positive; therefore, the perceived dominance in the +FE and +BM was not a negative impression. Dominance and being in charge can be related to impressions of competence, and previous studies have shown that positivity and competence are inversely correlated (Cuddy et al., 2004; Fiske et al., 2007) in certain contexts. However, more recently, Kraft-Todd et al. (2017) showed that perceived competence, warmth, and empathy can be positively associated in health settings. Characteristics such as higher status (Campbell et al., 2006), competence (Howe et al., 2017), and professionalism (Williams et al., 2007; Daniali and Flaten, 2019), which are usually associated with impressions of dominance, have been shown to be associated with positive treatment outcomes and lower symptom reporting. Necka et al. (2021) in an online multi-study showed that participants chose photographs of caregivers that looked more competent, and the caregivers' rated competence predicted participants' expectations about hypothetical post-procedural pain. Kraft-Todd et al. (2017) showed that participants had higher ratings of warmth for photographs of caregivers who were perceived as more competent. However, in that study, competence was tested with photographs of caregivers in white lab coats. In the present study, we tested dominance and being in charge by means of NBs and showed that more positive facial expressions and body movements add to the amplitude of perceived dominance.

A positive tone of voice did not contribute to the perceived dominance, but it did contribute to the perceived overall positivity. Previously, Ambady et al. (2002b) showed that participants could correctly tell if their caregiver had been sued by listening to content-filter audio tapes of the caregivers. It was observed that dominance in tone of voice was correlated with filing lawsuits, whereas warmth in tone of voice was not. In line with previous studies, our results suggest that a warm tone of voice does not increase perceived dominance (Riess and Kraft-Todd, 2014).

Lastly, positivity, expressivity, and dominance are three important impressions of caregivers that can have substantial influences on treatment outcomes. Our results inform about the underlying NB structures that contribute to impressions of positivity, expressivity, and dominance, with implications for patient experience and treatment outcomes. A more detailed understanding of the role of micro-level NBs in the generation of positivity, dominance, expressivity, and perhaps other medically important impressions can shed light on how placebo effects emerge.

